### Mitigation Against Risk of Cerebral Herniation

#### Eligibility

From previous studies, we will use a conservative midline shift of 5 mm, as well as the ELD safety score, ELD will only be performed if safety score is ≥5 (Table 3).

**TABLE 3. T3:** ELD Safety Score^25^

Prepontine cistern	Quadrigeminal cistern	Uncal herniation	Foraminal herniation
Normal: 2	Normal: 2	Absent: 2	Absent: 2
Compressed: 1	Compressed: 1	One side: 1	
Not discernible: 0	Not discernible: 0	Both sides: 0	Present: 0

Total score ≥ 5: LP or LD feasible; ≤ 5: LP or LD not feasible.

#### ELD Drainage Pressure

ELD in patients without high ICP will be set at 15 mm Hg and those with high ICP at 20 mm Hg, with a maximum of 10 mL/h drainage of CSF.

#### ELD Drainage Volume

No more than 10 mL CSF will be drained within 1 hour in either intervention arms; this will be ensured by using the LimiTorr ELD system as described before.

#### STOP Criteria

ELD shall be discontinued if.Any patient has an acute herniation event within 1 hour of ELD placement and CSF drainageThere is a decrease of NPI <3 (the abnormal threshold) within 1 hour of ELD placement and CSF drainage that is not reversed by additional tier 1 therapies.The treating team deems continuation of ELD as a clinical risk to patient based on neuroimaging or clinical criteria.If legally authorized representative (LAR) withdraws consent for continuing study

### Adverse Events Reporting

#### Local Institutional and Central IRB

All critical neuroworsening events in intervention arms will be reported to the medical monitor who will make determination of expectedness, and if deemed unexpected will be further reported to local site institutional IRB, central IRB, and DSMB within 24 hours.

#### Data Safety and Monitoring Board

A DSMB of 4 experienced trauma neurosurgeons and neurointensivists of international standing will be constituted, who will review every suspected unexpected critical neuroworsening event, as defined above, in each arm of the study. All critical neuroworsening events will be reported to the medical monitor (a neurosurgeon) within 24 hours, who will review expectedness, and refer all unexpected serious adverse events (SAEs) to the DSMB. If an unexpected SAE is suspected, ongoing ELD CSF drainage will be paused. The DSMB will review all intervention-related critical neuroworsening events and present a decision to the steering committee within 48 hours. A minimum of 3 DSMB members will independently review SAE. If the DSMB concludes that a critical neuroworsening event was not related to intervention, participant may continue study procedures per protocol. If, however, DSMB deems a neuroworsening event to be related to intervention, and if a discrete contributing factor is identified, the steering committee will meet within 7 days to review the report and discuss necessary changes to protocol before further enrollment.

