## QUALITY ASSURANCE AND PROJECT MANAGEMENT

The trial operations are being performed by the Clinical Operations Division at MTBI,^2^, Bethesda. The group is composed of the Director of Clinical Operations, an operations manager, a trials manager, a regulatory operation personal, a safety and protocol adherence reviewer, and 2 information technology personnel. The PI and research fellow complete all activities in accordance with federal requirements. Site training and visits are undertaken by and under the supervision of the Clinical Operations Division staff, and biweekly meetings are held to review screening and screen failures. The steering committee meets every 2 months or more often as needed. Annual reports are submitted to the sponsor.

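### An event judged related to lumbar drainage has no stated steering committee meeting or enrolment consequence unless a discrete contributing factor is also identified

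*Protocol article*

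**What the plan says.** The section Data Safety and Monitoring Board describes a sequence of steps after a critical neuroworsening event.

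- **Referral.** Events go to the medical monitor, "who will review expectedness, and refer all unexpected serious adverse events (SAEs) to the DSMB".
- **Drainage in the affected patient.** "If an unexpected SAE is suspected, ongoing ELD CSF drainage will be paused".
- **DSMB review.** "The DSMB will review all intervention-related critical neuroworsening events and present a decision to the steering committee within 48 hours". At least three members review independently.
- **If judged unrelated.** "If the DSMB concludes that a critical neuroworsening event was not related to intervention, participant may continue study procedures per protocol".
- **If judged related.** The consequence applies when the event is deemed "to be related to intervention, and if a discrete contributing factor is identified, the steering committee will meet within 7 days". The purpose of that meeting is "to review the report and discuss necessary changes to protocol before further enrollment".

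Three other sections bear on the point. The STOP criteria list when drainage is discontinued in an individual patient. The section on local and central IRB reporting sends unexpected events in the intervention arms to the IRBs and the DSMB within 24 hours. Under Quality Assurance and Project Management, "The steering committee meets every 2 months or more often as needed".

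**The concern.** The only wording in the article that links a safety event to further enrolment applies when the event is both attributed to the intervention and explained. Harm attributed to external lumbar drainage (ELD) that nobody can explain is at least as strong a reason to stop and review, since no correctable cause has been found. The second condition leaves that case out of the scheduled review.

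This matters more here than in many trials. Safety, measured by neuroworsening events, is a primary aim. The Discussion expects that results may lead to changes in the protocol while the phase 1 trial is running. Trial Status reports four enrolling sites with three more expected, so an event at one site needs a dependable route to a decision covering all of them.

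**Working it through.** The point concerns the logic of a rule. No sample size, error rate or event rate enters, and there is no figure in the plan to reproduce. The check is to list the possible results of DSMB adjudication and read off what the text attaches to each.

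| DSMB finding | 7-day steering committee meeting | Stated link to further enrolment |
|---|---|---|
| Not related | None; the participant may carry on | None |
| Related, discrete factor identified | Yes | Yes |
| Related, no discrete factor identified | Not stated | Not stated |

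The next step is to ask whether any other section supplies the two missing entries in the last row.

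1. **The 48-hour DSMB decision.** It covers all intervention-related critical neuroworsening events and does not depend on a contributing factor, so review does take place in the third row. The text does not say what the decision may contain, or that enrolment waits for it.
2. **The drainage pause.** It starts when an unexpected SAE is suspected, again without reference to a factor. It concerns ongoing drainage, not enrolment.
3. **STOP criteria.** These discontinue the drain in an individual patient. They set no trial-level step.
4. **IRB reporting.** Unexpected events in the intervention arms reach the local IRB, the central IRB and the DSMB. The section covers reporting and states no enrolment consequence.
5. **Steering committee schedule.** The committee meets two-monthly and can convene sooner. That is discretionary and tied to no event.

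The two entries in the last row therefore stay empty. Even in the second row, the words "discuss necessary changes to protocol before further enrollment" imply that enrolment waits but do not expressly order a pause.

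**The case against.** The strongest case against the point has three parts.

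**The article is condensed.** Trial-level pause rules and the options open to a DSMB are commonly set out in a full protocol or DSMB charter, and neither is shown. Silence on them is no finding. This stands, and it rules out any complaint that the article lacks an event count or a formal stopping boundary. It does not dispose of the point, because the article prints a specific trigger with a specific limiting condition. The criticism is of that condition.

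**The clause may have a narrower purpose.** An identified factor is what gives the committee something concrete to change, so the sentence could be read as saying when a protocol-change meeting is useful. The steering committee will already hold the DSMB decision and may meet early. This is a fair reading of intent and it lowers the seriousness. But it leaves the response to an unexplained related event to discretion, while an explained one has a deadline.

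**Stronger readings fail.** A reader might infer that unexplained related events receive no review and no hold. The documents contradict this: DSMB review, the drainage pause, the STOP criteria and IRB reporting all operate without a contributing factor. A reader might also infer that such events could accumulate through every patient given ELD. That assumes the DSMB, the IRBs and the steering committee all stay passive, which nothing in the text supports. It also needs an allocation that the article does not give: the Randomization section describes two stages with no ratio, and its figure is not shown.

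The other side is also right that deleting the clause would not settle everything. The medical monitor refers only unexpected SAEs to the DSMB, while the same section says that the DSMB reviews all intervention-related events. A related event classed as expected might therefore never receive a ruling on relatedness.

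**Conclusion.** The point holds in a limited form. Followed as written, the rule requires the 7-day steering committee meeting before further enrolment only when a related event also has an identified discrete factor. A related event without one has no stated meeting and no stated enrolment consequence, although it remains under DSMB review and the patient-level and IRB safeguards.

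The size is one unassigned branch out of three. No number of patients or events should be claimed.

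The conclusion assumes that the article reproduces the operative rule. If the full protocol or a DSMB charter already covers the branch, the article only needs to be brought into line. This is a cheap improvement to safety oversight, not a sign that oversight is absent.

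**What to change.** Delete the contributing-factor condition from the trigger. Every event that the DSMB deems related to the intervention then leads to the steering committee meeting within 7 days and before further enrolment. Whether a discrete factor can be found becomes an agenda item that informs whether a protocol change is possible. It is no longer a condition for meeting.

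In the same edit, reconcile the sentence that refers only unexpected SAEs to the DSMB with the one that has it review all intervention-related events, so that the trigger can operate on the events it is meant to cover.

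The main change is one clause. Its downside is an occasional extra meeting and a short enrolment pause. It alters a governance step only and leaves drainage settings, discontinuation criteria and patient management untouched.

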## Follow-up

Follow-up for the study will be till 14 days since injury to determine 2-week mortality. Other outcomes will be measured during intensive care unit stay only.

## DATA MANAGEMENT AND STATISTICAL ANALYSIS

All data including screening, inclusion/exclusion criteria, e-consent, randomization, and clinical data from all patients will be collected directly into a centralized electronic case report form supported by the MTBI^2^ Collection, Access, Sharing, and Analytics (CASA) platform system based in Henry Jackson Foundation Bethesda. National Institute of Neurological Disease and Stroke TBI-related common data elements from the following domains will be used: patient characteristics and history, disease/injury-related events, assessments and examinations, treatment/intervention data, protocol experience, and outcomes and end points (32) (Table 4).

**TABLE 4. T4:** Common Data Elements Collected: Domains, Measures, and Instruments

Domain	Subdomain	Measures/instruments
Participant characteristics and history	Demographics	Age, race/ethnicity, sex/gender, socioeconomic status, military service
	General health history	Significant medical history
Disease/injury Related events	Classification	Baseline risk assessment
		Injury severity score
		Head AIS
	History of disease/injury event	Injury presentation^a^
		Type, place, cause and mechanism of injury
	Discharge information	Discharge destination, time, and vital status
	Second insults	Aspiration, cardiac arrest, hyperventilation, hypotensive episode, seizure
		EEG monitoring
Assessments and examinations	Physical/neurological examination	Glasgow coma scale
		Pupil size, shape, and reactivity
		neurological pupil index
	Vital signs and other body measurements	Height and weight
		ICP monitoring
	Imaging	Cranial CT data
	Laboratory tests	Laboratory results (including INR and platelet count)
Treatment/intervention data	Surgeries and other procedures	ER/admission therapeutic procedures
		Surgical and therapeutic procedures
		Intraoperative management
	Therapies	Therapy intensity level
	Drugs	Prior and concomitant medications
Protocol experience	Participant/subject identification, eligibility, and enrollment	Informed consent
	Off treatment/off study	Study discontinuation/completion
Outcomes and end points	Disability	Glasgow outcome scale
	Adverse events	Severity: common terminology criteria for adverse events v6.0
		Expectedness: NIA adverse event and serious adverse event guidelines
		Causality: NIA adverse event and serious adverse event guidelines
		Neuroworsening events

AIS, Acute Injury Severity; CT, computed tomography; ICP, intracranial pressure; INR, international normalized ratio.

a Date and time of injury, symptom onset, arrival to the hospital, emergency service response, first treatment, admission.

The secure database can only be accessed by personnel certified by the Informatics Division of MTBI^2^ using a secure access card and key. No data can be removed, only data pertaining to a subject being included in trial at any site can be viewed by that site's research personnel. Research team will not have access to the data until data lock is lifted. All patients will be assigned a Global Unique Identifier, and at the end of the trial, all data will be uploaded to the central Federal Interagency Traumatic Brain Injury Repository.

## OUTCOMES

### Primary Outcomes

Both “intention-to-treat” and “treated as per protocol” analyses will be performed. Incidence of critical neuroworsening events will be compared between each arm, and between both ELD groups and control arm. Univariate and multivariable analyses will be performed using baseline variables, hourly NPI change, and volume of CSF drained per day for outcomes, ie frequency of neuroworsening events and death. Multivariable analyses will use stated adverse outcomes as dependent variables, and age group, sex, baseline ELD safety score, and pupillary abnormality as independent variables. Logistic regression will be performed using those variables that have an association with outcome with a *P*-value of ≤.10.

For feasibility, a comparison between proportion of patients in each arm who underwent ELD as per protocol will be performed. Comparison between the 2 ELD groups will be performed. Interactions will be tested for in all analyses.

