**METHODS::**

The study will include 30 severe TBI patients with a Glasgow Coma Scale score ≤9 who will be randomized to usual treatment, usual treatment plus early ELD placement if initial ICP ≤20 mm Hg, or late ELD if ICP ≥20 mm Hg as first intervention in tier 2 of Seattle International Brain Injury Consensus Consortium protocol.

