### Randomization

The study will enroll 30 severe TBI patients who will undergo 2-stage randomization into usual treatment, usual treatment plus early ELD placement if ICP ≤ 20 mm Hg, or late ELD if ICP ≥ 20 mm Hg (Figure). The process of randomization will be centralized through a secure computerized site.

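### The neuroworsening comparison sets ELD groups defined by different ICP states against each other and against one undivided control arm, so ICP severity can be mistaken for an ELD effect

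*Protocol article*

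**What the plan says.** The Randomization section of the protocol article says: "The study will enroll 30 severe TBI patients who will undergo 2-stage randomization into usual treatment", with the other two options being "usual treatment plus early ELD placement if ICP ≤ 20 mm Hg, or late ELD if ICP ≥ 20 mm Hg". The Abstract (Methods) adds the timing of the late group: "late ELD if ICP ≥20 mm Hg as first intervention in tier 2 of Seattle International Brain Injury Consensus Consortium protocol". The section on expected outcomes of the study describes the two ELD groups as lying before and after the onset of intracranial hypertension, and its hypothesis is that ELD does not raise serious adverse events in either setting. The inclusion criteria speak of a first randomisation, which implies a later one. The randomisation figure is not available in the text reviewed, and no allocation ratio is stated.

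Under Outcomes, Primary Outcomes (in the statistical analysis section), the safety analysis is: "Incidence of critical neuroworsening events will be compared between each arm, and between both ELD groups and control arm". Intention-to-treat and per-protocol analyses are both planned. The multivariable model lists "age group, sex, baseline ELD safety score, and pupillary abnormality as independent variables". Neither ICP nor randomisation stage is on that list, and only one control arm is mentioned.

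**The concern.** Randomisation protects a contrast only between patients who were eligible for the same randomisation at the same time. Patients in the late ELD group have raised ICP by definition. Early ELD patients did not have it when assigned. A single usual-treatment arm holds both kinds. If neuroworsening is more frequent when ICP is high, three things follow:

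- Early versus late compares different points in the disease course.
- Late ELD looks harmful against a control arm that includes patients whose ICP never rose.
- Depending on the scheme, early ELD can look better or worse than it is.

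Critical neuroworsening is the primary safety outcome, and a phase 2/3 trial is to be designed if ELD shows no increase in serious adverse events in either setting. A spurious excess could end the programme. A control arm weighted with sicker patients could mask real harm from early ELD.

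This is not a detail left to an analysis plan. The article states which groups are compared, and an analysis plan that followed it would carry the problem forward.

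**Working it through.** The plan gives no power, margin or arm-specific rate, so there is no figure to reproduce. The check is to compute expected event proportions by arm when ELD has **no effect**, and see whether the planned contrasts return zero.

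**From the protocol article:** 30 patients; early ELD at low ICP; late ELD at high ICP; one control arm.

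**Assumed:** event risk *l* at low ICP and *h* at high ICP, with *l* = 15% and *h* = 45% as the central case; share *f* = 50% with high ICP; allocation ratios as given below.

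**Reading A: usual-treatment patients who reach high ICP are re-randomised 1:1 to late ELD or continued usual treatment, and the three arms are formed by treatment finally assigned.**

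- Early = (1 − f)·l + f·h = 0.5 × 15% + 0.5 × 45% = 30%.
- Late = h = 45%.
- Control = [(1 − f)·l + (f/2)·h] / [(1 − f) + f/2] = (7.5% + 11.25%) / 0.75 = 25%.
- Late − control = +20 points; early − late = −15; early − control = +5.
- Pooled, one third early at stage 1 (10 early, 5 late, 15 control): (10 × 30% + 5 × 45%) / 15 = 35%, so +10 points.
- Pooled, 1:1 at stage 1 (15 early, 3.75 late, 11.25 control): (15 × 30% + 3.75 × 45%) / 18.75 = 33%, so +8 points.

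Taking *f* = 30%, 50% and 70%, risk pairs 20%/40%, 15%/45% and 10%/50%, and both stage-1 ratios, the spurious pooled difference runs from about +4 to +13 points.

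**Reading B: parallel ICP strata, 15 patients in each.**

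- 2:1 in both strata (10 early, 10 late, 10 control made up of 5 low and 5 high): control = (5 × 15% + 5 × 45%) / 10 = 30%. Early − control = −15; late − control = +15; early − late = −30. Pooled = (10 × 15% + 10 × 45%) / 20 = 30%, so 0.
- ELD to control 1:2 in the low stratum and 2:1 in the high stratum (5 early, 10 late, 15 control made up of 10 low and 5 high): control = (10 × 15% + 5 × 45%) / 15 = 25%; pooled = (5 × 15% + 10 × 45%) / 15 = 35%, so +10.

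**Null check.** With *l* = *h* = 22%, every difference is 0 under both readings. The bias arises only if risk differs by ICP.

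**With stage-matched comparators (Reading A, one third early).** Stage 1: early 30%, against all 20 patients not assigned early ELD, (10 × 15% + 10 × 45%) / 20 = 30%; difference 0. Stage 2: 5 late at 45% against 5 usual treatment at 45%; difference 0. Under Reading B, comparison within strata also gives 0.

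**The case against.** The strongest reply is that the scheme sits in a figure that is not available here. From this text a reader might infer that the pooled ELD contrast is certainly biased. The documents do not support that: with parallel strata and equal ratios its expected bias is zero. Two-stage randomisation and the mention of a first randomisation point towards re-randomisation without establishing it. Intention-to-treat might also keep re-randomised controls in their stage-1 group, but with two randomisations the term does not say which assignment counts. The wording on both ELD groups could also mean each separately against control; each would still face the same single control arm.

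Three further inferences should be resisted.

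- **The pooled contrast is the plan's main safety answer.** The article ranks no contrast, and its hypothesis concerns each setting.
- **A clock from injury shortens neuroworsening follow-up for second-stage patients.** "Follow-up for the study will be till 14 days since injury to determine 2-week mortality" concerns mortality; the next sentence confines other outcomes to the intensive care stay.
- **"Comparison between the 2 ELD groups will be performed" is a safety comparison.** It stands in the feasibility paragraph. The early-versus-late safety contrast comes from the comparison between each arm.

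It is also fair to say that chance dominates in 30 patients: for 35% versus 25% with 15 per group, the 95% half-width is 1.96 × √(0.35 × 0.65/15 + 0.25 × 0.75/15), about ±33 points. A wide interval shows imprecision, however, and does not reveal bias. Review of individual events by the safety board is valuable but does not repair the between-arm comparison.

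**Conclusion.** The concern holds for the comparisons as stated. Early versus late neuroworsening is not a randomised contrast, and late ELD against one mixed control arm is not like for like; both are true whichever way the two stages work. The pooled contrast is confounded only under re-randomisation with arms formed by final treatment, or under unequal ratios across strata.

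With no ELD effect and the assumed 15% and 45% risks, the spurious late-versus-control difference is +20 points under re-randomisation and +15 under parallel strata with 2:1 allocation. Early versus control is +5 and −15 respectively. Under re-randomisation the pooled difference is about +8 to +10, and +4 to +13 over the assumed grid. These figures show scale and are not predictions: the documents give no event rates by ICP, no share reaching high ICP and no ratios, and if risk did not vary with ICP the bias would vanish.

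**What to change.** Replace the comparison sentence with two contrasts that the randomisation supports:

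1. Early ELD versus usual treatment among all patients randomised at stage 1, by stage-1 assignment. Patients later re-randomised stay in their stage-1 group.
2. Late ELD versus usual treatment among patients randomised at stage 2, counting neuroworsening events from that randomisation.

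Obtain any overall ELD estimate by stratifying on stage, with an exact or Mantel-Haenszel method. Label the early-versus-late neuroworsening comparison descriptive.

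The change is to analysis wording. It needs no extra patients and leaves care unchanged, and the planned data already include randomisation and ICP monitoring. The cost is smaller groups per contrast: in the one-third-early illustration, stage 2 would compare about 5 with 5, so the late ELD estimate will be very imprecise and should be reported with its interval.

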### Intervention

ELD placement will be performed bedside or in operating room if patient is undergoing surgery but not under radiographic guidance and connected to the LimiTorr™ drainage system (Integra Neurosciences), and zero-leveled at the level of the tragus. The LimiTorr™ provides volume-limited drainage and shuts off at a maximum drainage of 10 mL/hour, by always leaving 10 mL of fluid in the 20 mL shut-off-burotrol. The burotrol will be primed with 10 mL of sterile water or saline and will only be drained to a maximum mark of 10 mL on the burotrol—stickers will be placed on the burotrol to ensure adherence to protocol. However, should overdrainage occur in a rare instance, the ELD will be clamped for 1 hour.

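### Daily CSF volume is used to predict neuroworsening and death, yet some of those events stop or pause drainage and no pre-event window is set, so the association is open to reverse causation

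*Protocol article*

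**What the plan says.** In the protocol article, the Primary Outcomes text of the analysis section states: "Univariate and multivariable analyses will be performed using baseline variables, hourly NPI change, and volume of CSF drained per day for outcomes", and defines the outcomes as "ie frequency of neuroworsening events and death". The next sentence lists the covariates of the multivariable model as "age group, sex, baseline ELD safety score, and pupillary abnormality as independent variables", without volume. Selection then follows: "Logistic regression will be performed using those variables that have an association with outcome with a" P-value of at most .10. No time window is given for volume. By contrast, the Secondary Outcomes text of the same section does set an order in time for NPI, taking the latest value before the event.

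Other sections let outcome events act on drainage:

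- **STOP Criteria.** ELD is discontinued if "Any patient has an acute herniation event within 1 hour of ELD placement" and drainage, if NPI falls below 3 in that hour and is not reversed, or, with no time limit, if the treating team sees a clinical risk in continuing.
- **Data Safety and Monitoring Board.** "If an unexpected SAE is suspected, ongoing ELD CSF drainage will be paused". The board decides within 48 hours, and a participant may continue if the event is judged unrelated.
- **Table 2.** Herniation syndrome and a new decrease in pupillary activity are themselves critical neuroworsening events, so these stop triggers overlap the endpoint.

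ELD Drainage Pressure sets the drain at 15 or 20 mm Hg according to ICP. ELD Drainage Volume caps it at 10 mL in an hour.

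**The concern.** A predictor should be fixed before the outcome it predicts. Here a patient who herniates, dies or has drainage paused for a suspected SAE can record a low daily volume because of the event. A daily total cannot separate drainage before the event from drainage lost after it. If controls enter the same analysis with zero volume, the variable also stands in for treatment arm.

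This is the only analysis the article describes that relates amount drained to harm. The trial is a phase 1 safety study whose results are meant to inform changes to its own protocol and the design of a phase 2/3 trial. A distorted association could hide a harm of larger volumes, or suggest a relation that does not exist.

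**Working it through.** The plan gives no figure for this association, so there is none to reproduce. The check asks how large a spurious difference can arise when volume has no effect.

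**Inputs from the protocol article.** Cap of 10 mL/h; 22% with new pupillary asymmetry in the registry analysis, used as an illustrative event rate; 30 patients; review within 48 hours; P ≤ .10.

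**Assumptions, not in the article.** 10 controls and 20 ELD patients; 5 planned drainage days (120 h); mean rate 5 mL/h, so 120 mL/day uninterrupted; event time uniform over the 120 h; rank-sum test at two-sided P ≤ .10. Let f be the share of events that stop drainage for good.

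**Step 1, range within a day.** The ceiling is 24 × 10 = 240 mL. A stop at hour 1, 6 or 12 limits that day to 10, 60 or 120 mL.

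**Step 2, ELD patients only, volume averaged over planned days.** A stopping event loses on average half the drainage, so the expected difference (event minus non-event) is -f × ½ × 120 = -60f mL/day. Simulation agrees:

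| f | -60f | Simulated mL/day | Trials that look protective (nominal 5%) |
|---|---|---|---|
| 100% | -60 | -60.3 | 78% |
| 50% | -30 | -29.3 | 31% |
| 25% | -15 | -14.5 | 15% |
| 10% | -6 | -6.1 | 8.5% |

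**Step 3, other readings of daily volume.**

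- *Drainage days only, f = 100%.* An event on day k gives 120 - 60/k. The mean loss is 60 × (1 + 1/2 + 1/3 + 1/4 + 1/5)/5 = 27.4 mL/day. Simulated: -27.2, with 34% of trials looking protective.
- *A 48 h pause, then resumption, planned days.* Hours lost are (72/120) × 48 + (48/120) × 24 = 38.4, which at 5 mL/h over 5 days is 38.4 mL/day. Simulated: -39.2. Over drainage days only: -5.5.
- *All events in the first hour.* About -118 to -120 mL/day, and nearly every trial looks protective.

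**Step 4, confounding in the other direction.** Drainage is pressure-set, so severity may raise both volume and risk. With a shared severity factor of 1.0 log-odds per SD:

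| f | Planned days, mL/day | Drainage days, mL/day |
|---|---|---|
| 100% | -41.7 | -2.3 |
| 50% | -5.0 | +13.8 |
| 25% | +12.7 | +22.6 |
| 10% | +23.7 | +26.7 |

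**Step 5, controls entered as zero while ELD truly doubles risk (22% to 44%).** Expected events are 10 × 0.22 = 2.2 in controls and 20 × 0.44 = 8.8 in ELD, so ELD supplies 8.8/11 = 80% of event patients. It supplies 11.2/19 = 58.9% of non-event patients. Mean volume is 0.8 × 120 × (1 - f/2) with an event and 0.589 × 120 = 70.7 without.

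- No stopping: 96 - 70.7 = +25.3 mL/day.
- f = 25%: 84 - 70.7 = +13.3 (simulated +14.2).
- f = 50%: 72 - 70.7 = +1.3 (simulated +0.8).
- f = 100%: 48 - 70.7 = -22.7 (simulated -22.0).

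A real harm is thus weakened, hidden or reversed as f rises.

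**Step 6, volume before the event per 24 h at risk.** Without severity confounding the difference is about 0 mL/day, with about 5% of trials passing P ≤ .10 in each direction. With confounding it is +8 to +30 mL/day, and about 9% to 31% of trials look harmful. A pre-event window therefore removes the reverse causation but not the confounding.

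**The case against.** A reader might infer that every neuroworsening event stops drainage and that the analysis is bound to make more drainage look protective. The documents do not support that.

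- The herniation and NPI rules cover only the first hour. The pause needs a suspected unexpected SAE and can be lifted. A motor-score drop or new motor deficit has no automatic stop of its own.
- The provision that "should overdrainage occur in a rare instance, the ELD will be clamped for 1 hour" responds to overdrainage, not to an outcome event, so it is no evidence that events determine dose.
- Step 4 shows that the sign can reverse.

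These limits stand and narrow the point to an exposure open to bias, with protection the probable direction.

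It can also be said that the exposure window and analysis set are usually left to a statistical analysis plan, which is not shown. That has some force: the article does not say that post-event volume counts or that controls enter as zero. But the article itself fixes the daily unit, the outcomes and the selection threshold, and it sets time order for NPI but not for volume. A window defined elsewhere would settle the matter; the specification as stated does not.

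Lastly, volume is neither an aim nor an outcome, and the covariate list that follows omits it, so its place in the final model is unclear. That limits the importance of the point. The univariate analysis is affected either way.

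**Conclusion.** The point holds in a limited form. As specified, the association of daily CSF volume with neuroworsening and death is open to reverse causation, probably towards apparent protection. In the illustrations without severity confounding, the spurious difference averaged over planned days ranges from -6 mL/day (10% of events stop drainage) to -60 mL/day (all do), and to about -120 if every event falls in the first hour. Strong severity confounding can bring it to +24 mL/day, or +27 over drainage days only.

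These figures rest on the assumed arm sizes, 5 drainage days, 5 mL/h and uniform event times. They show plausible size, not a forecast. What does not depend on them is that the coefficient cannot be read as a dose-safety relation in either direction.

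The randomized comparison of event incidence between arms, which is the primary safety analysis, is not affected.

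**What to change.** In the Primary Outcomes text of the analysis section, replace the daily-volume predictor with drainage accrued before the first neuroworsening event or death:

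- Define it as a time-varying or lagged exposure, for example mL per hour at risk. Event-free patients contribute their at-risk time to the same risk sets.
- Count drainage that resumes after a clamp or pause, provided it precedes the event. Dropping it would discard genuine exposure.
- Analyse ELD patients only, and keep volume out of any model that includes controls.
- Adjust for or stratify by prior ICP or by early/late ELD group, where event numbers allow.
- Label the result exploratory.

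The cost is mainly wording, and no clinical procedure changes. Drained volumes and event times must be time-stamped. The article's list of hourly monitoring and its Table 4 do not name drained volume, so the case report form should be checked. Using ELD patients only gives a less precise estimate, and with few events adjustment for ICP may not be possible, in which case residual confounding should be acknowledged.
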